**Fig. 4 Fig4:**

Schematic of the project timeline

Procedures are also in place to account for drop-out of participants. Should any young people drop out before the intervention has begun (prior to the one-to-one meeting with the group facilitator), the next consecutive student in the list will be invited to take their place (i.e. student 31, student 32, etc.) and baseline assessments will be conducted. On the other hand, any students who ‘drop-out’ between baseline assessment and intervention will be treated as ‘intention to treat’ and therefore will be invited to take part in the follow-up assessment even if they do not participate in the ReSET group.

For the integrity of the randomisation to be preserved, it is crucial that the allocation of young people to a treatment within a given school occurs *after* all eligible children from that school (and their parents) have been screened and consented to take part. If a child or a parent knew, at the point of baseline assessment and/or at the point of making the decision whether to take part, which treatment arm they would be signing up for, then participation would not be independent of randomisation. This would risk selection effects which have the potential to cause bias in the estimation of intervention effects. As such, we will screen the entirety of the participating year groups at the first screening timepoint, and students will only be informed which group they have been allocated to only after they have completed their baseline assessment. We expect modest increases in symptomology between the screening phase and the beginning of the third set of assessments in line with population-level changes to psychopathology during adolescence (e.g. [95]). However, it is vital to the randomisation procedure that participants and their parents consent to take part in the study *prior* to when randomisation takes place, which necessitates that we screen and consent participants in the top 25% of SDQ scores at a single timepoint. We will collect SDQ data at our baseline assessment in addition to this screening questionnaire, which will allow us to adjust for changes to general psychopathology between the first screening timepoint and when the participant completes the baseline assessment.

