#### The ReSET group intervention

ReSET is a manualised intervention (including cognitive-emotional training elements) delivered in a group-based setting with up to 10 adolescents allocated to each group. Sessions will be held weekly over an 8-week period and each session lasts between 90 and 120 min. The sessions will focus on developing adolescents’ understanding of the links between their social relationships, emotions, and mental health. Here, we describe the structure of our intervention that integrates the cognitive-emotional training tasks with psychoeducation about communication and mental health.

The intervention will begin with young people having an individual meeting with the group facilitator to discuss the aims of the groups, their goals for taking part, and any questions they have about the sessions. These individual meetings will be used to identify where the young person may be experiencing interpersonal difficulties that can be addressed in the group sessions. Issues arising from interpersonal difficulties will be set as explicit goals by the young person (with the aid of the facilitator), which will allow the young people to self-monitor their progress throughout the duration of the intervention.

Each of the group sessions will begin with participants completing the Child Outcome Rating Scale (CORS), a clinical measure designed to monitor an individual’s progress during the therapeutic process [52, 53]. The CORS measures several domains of the young person’s life functioning, including their individual wellbeing, interpersonal wellbeing, social role, and overall wellbeing [53]. The CORS has been validated with adolescents aged 11–15 [52]. Clinical cut-offs will be used by facilitators to identify young people who may need additional support during the group, or those that may benefit from more targeted services. The CORS will also be utilised during the intervention sessions to consider links between the strategies discussed in the sessions, their impact on how participants communicate with those around them, and the relationships between social interactions and wellbeing. Drawing links between social interactions and wellbeing will be a core component of the psychoeducation content of the intervention, particularly in relation to communication.

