## Assignment of interventions

### Timing of randomisation

Randomisation will be performed at each school once that school has been provided with a list of participants scoring within the top 25% (i.e. above the cut-off score of 15) of the sample from both year groups. All eligible students will be invited to participate, and students will be randomised in each year group in a numerical order: (a) 1–10 (Group 1)—Term 1, (b) 11–20 (Group 2)—Term 2, and (c) 21–30 (Group 3)—Term 3. As our intervention runs over two academic years in some schools (April 2023–March 2024), some cohorts will transition to the next academic year before the completion of the intervention. For example, the group that is in year 7 when the school is randomised will be in year 8 during the final intervention group run in that school (January–March 2024).

A random selection of eligible adolescents will subsequently be invited to participate in the main study. Parents will receive consent forms detailing the aims of the study, the structure of the intervention and the time commitment expected of participants (see Additional file 1: Appendix), which will also include a consent form. Once parental consent has been obtained, participants will be randomly allocated to one of the three school terms (i.e. the sample will be split into thirds with one third taking part in term 1, a second third taking part in term 2, and the final third taking part in term 3). At the beginning of the allocated term, consent will be sought from the young person, and they will complete the assessment battery comprising of mental health, emotion processing and social relationship measures (see Fig. 4). Participants allocated to the intervention arm of the study will then complete 10 sessions inclusive of individual pre-group sessions, 8 weekly group sessions, and a mid-group session. Participants allocated to the control arm of the study will complete their usual classroom schedule.

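### The two drop-out rules overlap: a pupil lost after baseline but before the one-to-one meeting is both replaced and kept as intention-to-treat, in the very window where the arm is disclosed

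*Protocol article*

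**What the plan says.** The drop-out procedure stands in the protocol article under Assignment of interventions, Timing of randomisation, in the text after the Fig. 4 caption.

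- Replacement rule: "Should any young people drop out before the intervention has begun (prior to the one-to-one meeting with the group facilitator), the next consecutive student" on the list is asked to fill the vacancy and then has a baseline assessment.
- Retention rule, introduced as the contrasting case: students who leave "between baseline assessment and intervention will be treated as ‘intention to treat", and they are invited to follow-up even if they never attend the group.
- Disclosure: "students will only be informed which group they have been allocated to only after they have completed their baseline assessment".

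The order of events comes from two other places. Timing of randomisation puts the assessment battery at the start of the allocated term and continues: "Participants allocated to the intervention arm of the study will then complete 10 sessions inclusive of individual pre-group sessions". The description of the ReSET group intervention says: "The intervention will begin with young people having an individual meeting with the group facilitator". For the other arm, the text says only: "Participants allocated to the control arm of the study will complete their usual classroom schedule".

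**The concern.** The two rules are meant to divide drop-outs into those who are replaced and those who are retained. As written they do not divide them, because one ends at the facilitator meeting and the other begins at baseline, which is earlier.

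The overlap sits at a sensitive point. A pupil could complete baseline, learn the arm, decline, and be replaced under the first rule. Whether that pupil stays in the trial would then depend on knowing the arm. The same section explains that participation must not depend on the allocation, because otherwise the effect estimate is open to selection bias. The drop-out rule permits what that explanation warns against.

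It also leaves open who belongs to the primary comparison when this happens: the leaver, the replacement, or both.

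**Working it through.** The point is settled by setting the rules against the order of events. No formula is needed for it.

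**1. Order of events in the intervention arm.** Baseline battery, then disclosure of the arm, then the individual meeting with the facilitator (the start of the intervention), then the group sessions.

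**2. Each drop-out period against the two rules.**

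| Pupil leaves | Replacement rule | Retention rule |
|---|---|---|
| Before baseline | applies | does not apply |
| After baseline, before the one-to-one meeting | applies | applies |
| After the meeting, before the first group session | does not apply | applies only if the intervention is taken to start with the group |

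The middle row is the collision. It remains whichever event marks the start of the intervention in the retention rule, because the span from baseline to the meeting lies inside both versions of that window. It would vanish only if the meeting came before baseline, which the stated order excludes.

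**3. Disclosure.** The arm is revealed after baseline, so disclosure can precede a departure in the middle row. A replacement called up at that point enters after the arm of the year group has been made known to at least one pupil in it.

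**4. Control arm.** No facilitator meeting is described for controls. The event that ends the replacement window therefore has no counterpart there, and the window cannot be dated.

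**5. The plan's own figures.** Sample size calculation: 540 × (1 − 0.20) = 432, as stated. Using the plan's ICCs (0.05 group, 0.02 year), r = 0.5 and clusters after loss of 8 per group and 24 per school year:

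- design effect, intervention: 1 + 7 × 0.05 + 23 × 0.02 = 1.81
- design effect, control: 1 + 23 × 0.02 = 1.46
- variance: (1 − 0.5²) × (1.81 + 1.46)/216 = 0.01135, SE = 0.1066
- power at two-sided 0.025: Φ(0.4/0.1066 − 2.241) = 93.5%, against 92.8% stated

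The replacement rule enters none of these figures.

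**6. Size of a possible bias.** The document gives no drop-out rate for the window and no difference between leavers and replacements. The following shows only how far the answer turns on the ambiguity. Assume that 5–10% of the 270 intervention pupils (13.5–27) leave in the window and are replaced, and that they differ from their replacements by 0.5 SD. Both are assumptions, and baseline adjustment is ignored.

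- Leaver removed from the analysis: 0.05 × 0.5 = 0.025 SD to 0.10 × 0.5 = 0.050 SD, which is 6–12.5% of δ = 0.4.
- Leaver kept and replacement added, at 5%: 13.5/270 × 0.5 − 13.5/283.5 × 0.5 = 0.0250 − 0.0238 = 0.001 SD, about 0.3% of δ.
- The same at 10%: 27/270 × 0.5 − 27/297 × 0.5 = 0.0500 − 0.0455 = 0.005 SD, about 1% of δ.

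The two readings of the rules differ by a factor of roughly 10 to 20 under identical assumptions.

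**The case against.** The best defence is that the authors meant baseline as the divider: before it, replace; after it, retain. The two sentences are framed as alternatives, the newcomer's baseline is mentioned as the next step after replacement, and the paragraph that follows states the principle that participation must be independent of allocation. This may well be the intention. But the parenthesis names the one-to-one meeting as the cut-off, and the defence works only by disregarding it. Staff who follow the text may replace a pupil after disclosure.

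A second defence is that analysis sets belong to the statistical analysis plan, which is not shown. That is fair as far as defining the set goes. The replacement rule, however, is operational: it is applied when a pupil leaves, and a later plan can classify a replacement but cannot undo it.

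Two stronger readings are tempting and are not supported:

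- A reader might infer that only intervention pupils can be replaced. The rule speaks of any young people, and each year group has a numbered list, so controls are not excluded. What is missing for them is the event that dates the cut-off.
- A reader might infer a bias of 6–12% of δ in a known direction. That needs an assumed rate, an assumed difference and removal of the leaver from the analysis, which the retention rule rules out. Nothing shows whether leavers would do better or worse than replacements. Each replacement also has a baseline, so the planned adjustment for baseline score would absorb part of any difference.

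**Conclusion.** Wrong as written. The overlap follows directly from the text and from the stated order of events, and it rests on no assumption about the data. Because the arm is disclosed inside the overlapping window, replacement there can depend on allocation and could differ between arms, more so as the window has no defined end for controls.

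The documents do not show that biased replacement will occur, and they do not allow its size or direction to be computed. The finding is therefore a contradictory rule at a point where selection can enter. It is not a demonstrated bias, and it does not call the sample size or power into question.

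**What to change.** - Delete the one-to-one meeting as the replacement cut-off.
- Allow replacement only before the leaver has completed baseline and been told the arm, by the same rule and from the same ordered list in both arms.
- Keep everyone with a completed baseline in the arm of their year group, invite them to follow-up and analyse them there, whether or not they attend.
- If a place freed after disclosure is filled so that a group can run, exclude that replacement from the primary analysis set, and report such replacements by arm and timing.
- If replacements have already been made under the present wording, settle their status before the analysis begins.

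The cost is a change of wording. The downside is that a few groups may have slightly fewer than 10 analysed pupils. The sample size calculation already assumes up to 20% loss, or 8 analysed pupils per group of 10, so this is covered as long as total loss stays within that allowance.

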### Randomisation schedule

Randomisation will be carried out in randomly permuted blocks of size 2. Each block has two elements:Cohort1-INT: Year 7 cohort receives the intervention, Year 8 cohort is the control groupCohort2-INT: Year 7 cohort is the control group, Year 8 cohort receives the intervention

A statistical programme to generate a randomised list of permuted blocks will be written by the project statistician, PM, using the R Software for Statistical Computing. This programme will then be used by an independent statistician not involved in the study to generate a randomised list. The independent statistician will use a new seed number to generate the list, and pass this on to the trial manager, LL. The trial manager will use the list to allocate year groups to treatment arms, going down the list in the order in which schools are ready to be randomised (see Additional file 1: Appendix for R script).

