### Eligibility criteria

Eligible participants will include pupils who are initially in years 7–9 (ages 11–14) at the time of the first baseline assessment, with each school running the study across 2-year groups only (i.e. either years 7 and 8, or years 8 and 9). We will seek consent from parents or carers, and the participant before they are enrolled in the study. Young people at *elevated risk* of mental health problems will be invited to participate, where *elevated risk* is operationalised as having a self-reported SDQ Total Difficulties score of 15 or higher in our screening assessment. This corresponds approximately to selecting the top 25% of this age group in the UK (see ‘Outcomes,’ below for a description of this measure). This estimate is based on self-reported SDQ scores from 2100 UK adolescents aged 10–15 derived from the Understanding Society panel survey (see [51]). The 75th percentile of the SDQ Total Difficulties Score in this sample was 15. Students will be considered ineligible if they have high rates of school absence or are identified by the school as being inappropriate for the group intervention due to a high risk of harm to self or others. We will not exclude participants on the basis of neurodivergence, such as Autism and ADHD, though pre-existing diagnoses will be recorded during the study, as will participants’ use of other mental health services.

Schools will be eligible to participate if more than 30% of their pupils qualify for free school meals (Department for Education, 2022). We chose this criterion to ensure socioeconomic diversity in our sample. A record of study sites can be found at: https://www.isrctn.com/ISRCTN88585916.

Facilitators will be mental health professionals either working for schools (e.g. school counsellors) or mental health professionals that provide services within schools from external agencies (e.g. NHS Educational Mental Health Practitioners). All facilitators will attend a 2-day training course (delivered by the clinical lead, RL, and a member of the research staff, AL) to provide them with information about the intervention, opportunities to roleplay group sessions, and training on how to administer the cognitive training tasks. Facilitators will have weekly supervision with the clinical lead, RL, throughout the duration of the intervention.

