### Blinding

Researchers conducting any assessments with participants will be blind to the allocation. Should any researchers become unblind to the allocation (e.g. due to a disclosure by a school staff member), this information will be recorded and reported with the trial outcomes. Only the independent statistician, researcher coordinator and PIs will have knowledge of the school allocation. The primary analysis will be conducted by the project statistician. A fully blinded analysis is not possible because of the partially clustered data structure (intervention participants are clustered within their groups, while control group members are not).

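### The trial manager is given the whole allocation list, in fixed blocks of two schools, so a coming school's allocation can be known while its recruitment is still open

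*Protocol article*

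**What the plan says.** Randomisation schedule (protocol article) sets the method: "Randomisation will be carried out in randomly permuted blocks of size 2". Each block holds two elements, one giving the intervention to the Year 7 cohort and one to the Year 8 cohort, so a block covers two schools. On custody of the list: "The independent statistician will use a new seed number to generate the list, and pass this on to the trial manager". On its use: "The trial manager will use the list to allocate year groups to treatment arms, going down the list in the order" in which schools become ready.

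Timing of randomisation describes the moment of allocation in two ways. It opens with "Randomisation will be performed at each school once that school has been provided with a list of participants scoring within the top 25" per cent, and then has a random selection of eligible pupils invited, with parental consent after that. Further on, the same section calls it crucial that allocation within a school follows screening and consent of all eligible pupils. It warns that if families knew the arm beforehand, "participation would not be independent of randomisation". It also states that pupils learn their arm only after baseline, and that a pupil who drops out before the intervention begins is replaced by the next one on the list.

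Blinding states: "Only the independent statistician, researcher coordinator and PIs will have knowledge of the school allocation". The trial manager is not named there.

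Eligibility criteria allows two pairings of years: "with each school running the study across 2-year groups only (i.e. either years 7 and 8, or years 8 and 9". The list elements mention Years 7 and 8 only.

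**The concern.** An independent statistician adds concealment only if the sequence stays with that person until a school's recruitment is fixed. Here the sequence moves to the person who applies it. Putting consent before allocation protects pupils and parents, but it does not conceal the result from whoever already holds the list.

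Both arms sit in every school, so foreknowledge cannot decide whether a school gets the intervention. It does reveal which of the school's two year groups will get it. Any difference between the two years in invitation, follow-up of consent, closing of the list or replacement falls directly on the treatment contrast. Adjustment for baseline score and school year (Primary outcome analysis) would not remove selection on unmeasured factors such as motivation.

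**Working it through.** **Inputs.** Nine schools (Sample size, Preliminary considerations). Fixed block size 2, with one element of each kind per block (Randomisation schedule). The list is held by the trial manager (same section). The plan gives no figure for predictability, so there is none to reproduce. Its stated power of 92.8% does not enter the check and is not changed by it.

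**Someone holding the list.** Every entry is visible: 9/9 = 100% known in advance.

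**Someone without the list who knows the block size and the earlier allocations in order.** The second school of each pair must take the element that the first did not.
- Schools known with certainty: numbers 2, 4, 6 and 8, so 4/9 = 44%. The ninth school opens a new block and cannot be deduced.
- Expected correct guesses: 4 × 1 + 5 × 0.5 = 6.5 of 9, or 72%. A simulation of 20,000 sequences averaged 6.495. Pure guessing would give 9 × 0.5 = 4.5 of 9, or 50%.

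The block size is printed in the article, and Blinding names the researcher coordinator and PIs as knowing the allocation. They are in this second position at least.

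**Is recruitment still open when the result is knowable?**
- The list exists before the later schools on it are screened, so its holder has the answer throughout their recruitment.
- On the opening account in Timing of randomisation, a school is allocated once it has its list of screen-positive pupils, and invitation and parental consent follow. Recruitment is then open even after allocation.
- On the later account in that section, consent comes first. This keeps families unaware, but not the list holder.
- On either account, drop-outs before the one-to-one meeting are replaced by inviting further pupils. Groups run over as many as three terms, so some replacement can come after the school has been allocated.

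**Who knows?** Randomisation schedule has the trial manager make the allocation. Blinding limits knowledge of it to three roles and does not name that one. The two agree only if trial manager and researcher coordinator are the same role, which the article does not say.

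**The case against.** The strongest defence is that the route to bias is narrow. School staff send the consent forms (Consent and assent procedures), and the article gives neither the trial manager nor the PIs a part in inviting or consenting pupils. Whole year groups are screened against a fixed self-reported SDQ cut-off, places follow a numerical order, replacement takes the next pupil on the list, and outcome assessors are blind. The 44% applies only to people who know earlier allocations and their order, and nothing suggests that school staff do. The article is condensed, and its appendix is not shown. All of this stands and limits the weight of the point. It does not remove the point, because the hand-over of the list is stated outright and no safeguard accompanies it.

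Four stronger readings are tempting, and the article does not support them:
- *Readiness has no criterion.* Timing of randomisation gives two. The trouble is that they conflict.
- *Each school is 60 of 540 pupils (11%), so steering one school shifts a material share of the trial.* Under Trial design, every school gives one cohort to each arm. Changing a school's list entry swaps the year groups and leaves the split between arms as planned. The 11% is not a measure of bias.
- *The labels give opposite allocations in Year 8/9 schools.* Trial design speaks of a younger and an older cohort in each school, and the elements are called Cohort1 and Cohort2, which largely settles the meaning. Clearer wording is worthwhile, but this is not a concealment failure.
- *Blocks of 2 must go.* They keep the younger/older balance while schools enter on a rolling basis. Keeping them is a reasonable trade-off.

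**Conclusion.** The point holds as a weakness in allocation concealment. As written, the list holder can know 9 of 9 allocations ahead of time, and staff aware of past allocations can deduce 4 of 9, while invitation, consent or replacement may still be open in the school concerned. This rests on the article's own account of custody and block size, on nine schools being randomised, and on no unstated sealing or staged release.

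The size of any resulting bias cannot be derived from the article. A reader might infer that selection was steered, or that the trial manager influenced consent. Neither is stated or shown. Sample size and power are unaffected. The conflicts on timing and on who knows the allocation are real and need reconciling. Overall this is a cheap improvement.

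**What to change.** 1. In Randomisation schedule, have the independent statistician keep the list. That person releases one school's allocation at a time, only after receiving the school's locked, dated list of eligible and consented pupils for both year groups. If the pupil order is locked with it, replacements also follow an order set before allocation.
2. Reconcile the two accounts in Timing of randomisation of whether invitation and consent come before or after allocation.
3. Reconcile Randomisation schedule with Blinding on whether the trial manager knows the allocation, and say whether trial manager and researcher coordinator are one role.
4. Word the two list elements as younger cohort and older cohort, so that they also fit Year 8/9 schools.
5. For schools already allocated, report the dates of list closure and of allocation. Trial status gives recruitment from March 2023 to about March 2024, so for some schools this may be all that can still be done.

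The cost is one request per school to a statistician already in the plan, plus text edits. With blocks of 2 kept, staged release cuts what the trial manager can know for certain in advance from 9 of 9 to 4 of 9, not to zero. The reported dates let readers judge what remains.
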